### Data analysis

Intention-to-treat (ITT) and per-protocol analyses will be performed for all effectiveness analyses with the ITT analysis considered as the primary method. The ITT analysis will include all patients that participated in the intervention regardless of adherence. Every effort will be made to minimize missing data and participant drop-out or loss to follow-up during the study period. We have accounted for possible drop-out or loss to follow-up by increasing the sample size by 20% in all groups. The “last value carried forward” approach will be used to fill in missing outcome variables; this approach reflects an analysis of the last known value of the outcomes and is thought to be conservative as far as the impact on the treatment effect. If the amount of missing data for outcomes or potential confounders is substantial (i.e., >10%), we will perform an analysis based on multiple imputation for comparison. We will also examine the pattern of missing data in order to discern whether the missing data mechanism could be non-ignorable. A per-protocol analysis will include only those participants who are considered to be adherent to the protocol as defined below.

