#### Analyses of Treatment Phase data

The primary hypothesis is that yoga is non-inferior to PT for our co-primary endpoints: reduction in back pain intensity and improvement in back-related function. First, a one-sided α = 0.05 level two-sample *t*-test will be used to determine if yoga is non-inferior to PT for the co-primary outcomes of pain and function. The mean differences between groups with corresponding standard errors, confidence intervals, and *P* values will be reported. While pain and RMDQ outcomes may have a tendency to be skewed, we are examining the change from baseline to week 12 in these scales as primary outcomes which are expected to have more normally distributed values. However, underlying assumptions of the *t*-test and regression models, including normality, will be examined. If important violations are found, then alternative methods will be explored including non-parametric methods. If any imbalance between groups is found in the preliminary analysis of the success of randomization, these variables will be used in regression models to adjust results, with change from baseline to week 12 with pain or function as the outcome, and treatment group and other potential confounders as predictors.

The following variables will be considered as possible effect modifiers for the relationship between treatment group and the outcomes of pain and function: study site, expectation of helpfulness, preference for treatment assignment, and depression. A multiplicative interaction term between treatment and the possible effect modifier of interest will be included in a regression model. If a significant interaction occurs, we will examine whether it is quantitative (e.g., two subgroups differ in the magnitude of effect, but the effect for both are in the same direction) or qualitative (i.e., two subgroups differ in the direction or interpretation of effect) in nature. We will also examine the secondary outcome of pain medication use during the previous week assessed at 12 weeks. Logistic regression with indicators for treatment and adjustment for possible confounders, including baseline medication use, will be used to compare medication usage rates between the yoga and PT groups. Medication subtypes including non-steroidal anti-inflammatory drugs, acetaminophen, opiates, muscle relaxants, and others will also be compared. Odds ratios with corresponding confidence intervals and *P* values will be reported.

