#### Analysis of Maintenance Phase data

For the Maintenance Phase, we hypothesize that i) maintenance yoga will be non-inferior to maintenance PT; ii) maintenance yoga will be superior to no yoga maintenance; iii) maintenance PT will be superior to no maintenance PT; and iv) maintenance yoga and maintenance PT will both be superior to education. To test our hypotheses, we will perform longitudinal analyses on the pain and function outcomes incorporating all measurements across the study period, including baseline and 6, 12, 26, 40, and 52 weeks. We will perform a longitudinal profile analysis to compare the pattern of change in outcomes over the study period with a five-part treatment variable (yoga maintenance, yoga no maintenance, PT maintenance, PT no maintenance, education), time, and their interaction as predictors in the model. The initial model will assume an unstructured covariance to account for the correlation between repeated measures on an individual. A simpler model may be used for the covariance or the model for the means over time if found to be appropriate. No missing data will be replaced in these longitudinal analyses. All available patient data can be included and the analysis will be considered to be unbiased under a “missing at random” mechanism. Additional subgroup longitudinal analyses can be done using only data from those participants who were 12-week completers. We will also compare the change in pain medication usage over time using a generalized estimating equation approach or non-linear mixed effects model to account for the repeated measures of a dichotomous outcome. This approach will parallel the longitudinal analyses for continuous outcomes described above.

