#### Sample size considerations

For the co-primary endpoints of change in pain or function from baseline to week 12, we assume a one-sided α error = 0.05. If we assume a minimal clinically significant difference of 2.0 points for the 11-point pain intensity scale, then using a 1.0 point non-inferiority margin for pain is reasonable [103]. If we assume 3.0 points on the 23-point RMDQ scale is a minimal clinical significant difference, then choosing a non-inferiority margin of 1.5 for function is reasonable [105]. A common standard deviation of change in all groups is 2.5 points for the 11-point pain intensity scale and 4.35 points for the 23-point RMDQ function scale [24,26].

Using these assumptions, 108 participants in both the yoga and PT group would provide 90% power to detect whether yoga is truly non-inferior to PT in respect to effect on pain. Similarly, 107 participants in both the yoga and PT group would provide 81% power to detect whether yoga is truly non-inferior to PT in respect to effect on function. Using these sample sizes, we would be able to detect at least a 1.4 unit difference in pain or at least a 2.4 difference in function with 90% power for superiority of yoga or PT compared to education. We inflated these sample sizes in order to protect against an estimated dropout rate of 20%. With this adjustment, the target sample size for the yoga and PT groups is 128 participants each. Using a yoga:PT:education 2:2:1 randomization scheme, we need a total of 320 participants (128 yoga, 128 PT, 64 education). Thus, for the co-primary outcomes of pain and function at 12 weeks, we have adequate power to determine non-inferiority between yoga and PT and superiority of yoga and PT to education*.*

We also anticipate adequate power for the longitudinal analyses of the Maintenance Phase data. Incorporation of repeated measures over time increases power by increasing the “effective sample size,” which is a function of the number of participants and the number of total measurements (0, 6, 12, 26, 40, and 52 weeks). Participants who drop-out or who have missing data can still be included in these analyses.

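### Last value carried forward is the primary missing-data method and is called conservative, but that reason does not hold for the primary yoga–PT non-inferiority test

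*Protocol article*

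**What the plan says.** The Data analysis section of the protocol article makes intention-to-treat the primary approach. It fills missing outcomes by LOCF, with the reason that this "is thought to be conservative as far as the impact on the treatment effect". Multiple imputation is run only as a comparison, and only if more than 10% of the data are missing. The section also commits to examining whether missingness could be non-ignorable and to per-protocol analyses.

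The section on Treatment Phase analyses states: "The primary hypothesis is that yoga is non-inferior to PT for our co-primary endpoints". The test is a one-sided two-sample t-test at 0.05 on change from baseline to week 12. The comparisons with education are two-sided superiority tests. Nothing exempts the non-inferiority test from LOCF or gives it a separate justification.

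The sample size section plans for 20% dropout and 128 participants in each of the yoga and PT arms. For the 52-week longitudinal model, the Maintenance Phase section says: "No missing data will be replaced in these longitudinal analyses". That model relies on missing at random and starts from an unstructured covariance.

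**The concern.** Whether a missing-data method is conservative depends on the hypothesis. In a superiority test, shrinking the difference works against the claim. In a non-inferiority test, the claim is that yoga is not worse than PT by as much as the margin, so shrinking a real deficit works in favour of the claim.

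Only two values can be carried to week 12: baseline, which means zero change, and week 6. If either shows less separation between the arms than week 12 would have shown, the filled-in data make the arms look more alike.

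At stake is the 5% error rate of the trial's primary claim. The stated safeguard would not show this, because multiple imputation is only a comparison. The protocol plans for 20% dropout, so it expects to pass its own 10% threshold and still keeps LOCF primary.

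**Working it through.** **Inputs from the sample size section.** Error rate: "we assume a one-sided α error = 0.05". Margins: "using a 1.0 point non-inferiority margin for pain is reasonable" and "choosing a non-inferiority margin of 1.5 for function is reasonable". Variability: "A common standard deviation of change in all groups is 2.5 points for the 11-point pain intensity scale and 4.35 points" for function. Expected dropout is 20%, with 128 randomised to each of yoga and PT. The Data analysis section applies the dropout allowance equally to all groups.

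**Assumptions, not in the documents.** f is the share of the week-12 effect present in the carried value: 0 if baseline is carried, and 0.5 or 0.75 as illustrations for week 6. The PT mean improvement μ is 2.5 (pain) and 4.0 (function). Carried week-6 values have the same SD and correlate 0.6 with week 12. Dropout is unrelated to any data, that is, completely at random.

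**Step 1: reproduce the plan's figures.** The protocol says "108 participants in both the yoga and PT group would provide 90% power" for pain, and 107 per arm with 81% for function.
- Pain: 1.0 / (2.5 × √(2/108)) = 2.939; 2.939 − 1.645 = 1.294; power 90.2%.
- Function: 1.5 / (4.35 × √(2/107)) = 2.522; 2.522 − 1.645 = 0.877; power 81.0%.

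Both agree, so the inputs are read correctly.

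**Step 2: shrinkage with equal dropout.** With dropout d in both arms and a true deficit equal to the margin M, the expected deficit after LOCF is M × [1 − d(1 − f)].

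The false non-inferiority rate is approximately 1 − Φ(1.645 − d(1 − f)M / SE), with SE = SD × √(2/128). That gives SE = 0.3125 for pain and 0.544 for function.

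Example (pain, d = 0.20, f = 0): the expected deficit is 0.80; 0.20/0.3125 = 0.64; 1 − Φ(1.005) = 15.7%.

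| Endpoint, d = 20% | f | Expected deficit | Formula | Simulated (20,000 trials) |
|---|---|---|---|---|
| Pain | 0 | 0.80 | 15.7% | 17.0% |
| Pain | 0.5 | 0.90 | 9.3% | 9.3% |
| Pain | 0.75 | 0.95 | 6.9% | 6.6% |
| Function | 0 | 1.20 | 13.7% | 14.0% |
| Function | 0.5 | 1.35 | 8.5% | 8.7% |
| Function | 0.75 | 1.43 | 6.6% | 6.9% |

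The formula holds the SD constant. Carrying zeros also reduces the spread somewhat, so the simulated pain figure at f = 0 is a little higher. With no dropout the simulated error is 5.1% (pain) and 4.9% (function). A separate simulation with μ = 2.3 for pain gave 16.7% (pain) and 14.6% (function) at f = 0. In that run, using observed week-12 values only kept the error at about 5%, so the excess comes from LOCF.

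At 10% dropout in each arm, the formula gives 9.3%, 6.9% and 5.9% (pain) and 8.5%, 6.6% and 5.8% (function) for f = 0, 0.5 and 0.75.

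**Step 3: unequal dropout.** With dropout dY in yoga and dP in PT, the expected deficit is M[1 − dY(1 − f)] + μ(1 − f)(dY − dP). Example (pain, f = 0, dY = 25%, dP = 15%): 1.0 × 0.75 + 2.5 × 0.10 = 1.00, so there is no net bias. Simulated error for f = 0:

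| Yoga / PT dropout | Pain deficit | Pain error | Function deficit | Function error |
|---|---|---|---|---|
| 25% / 15% | 1.00 | 5.2% | 1.53 | 4.1% |
| 30% / 10% | 1.20 | 1.0% | 1.85 | 1.0% |
| 15% / 25% | 0.60 | 37.8% | 0.88 | 33.4% |

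**The case against.** The strongest reply is that both direction and size are conditional.

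- **Direction.** A reader might infer that LOCF always favours non-inferiority here. It does not. Moderately more dropout in yoga cancels the bias, and a larger imbalance reverses it. A week-6 difference larger than the week-12 difference would also reverse it. The protocol supports equal dropout only as a planning allowance, and weekly group classes and individual sessions need not lose people equally. This stands.
- **Size.** A reader might take 17% and 14% as the error rates. They need every dropout to lack a week-6 value. The protocol schedules a week-6 survey with a telephone option, and it limits the intention-to-treat set to those who took part in the intervention, which may remove the earliest losses. With week-6 values carried, the rates are about 7–9%. If dropouts truly drift back towards baseline, the real effect is itself diluted and LOCF is less biased. This stands too, so only a range can be given.
- **Standard error.** A reader might add that single imputation understates the standard error. In this set-up it does not: each participant contributes one independent change score, so the t-test standard error is right for the LOCF estimator. For pain with baseline carried, the empirical SD of the difference and the mean estimated standard error were both 0.294; for function they were 0.514 and 0.513. The inflation is bias.
- **Contradiction.** A reader might say that the 52-week model contradicts the 12-week analysis. It is a separate analysis with a five-level treatment variable, and using a different method there is permissible.
- **Safeguards.** At the planned 20% dropout the multiple imputation is in effect certain to be run. With the missing-pattern review and the per-protocol analysis, it could expose a result driven by LOCF. But none of these replaces LOCF as the primary analysis.

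**Conclusion.** The point holds in conditional form. LOCF is the primary method for the 12-week outcomes, and the reason given for it fits at best the superiority tests against education. For the yoga–PT non-inferiority test, with similar dropout and carried values that separate the arms less than week 12 does, LOCF tends to shrink a true deficit and so favours declaring non-inferiority.

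With 128 per arm, 20% dropout in each arm unrelated to outcome, and a deficit equal to the margin, the nominal 5% becomes about 7–17% for pain and 7–14% for function. Where in that range depends on f and on mean improvement, which the documents do not give. The rates are per endpoint; a rule requiring both endpoints would lower the joint rate. Under unequal dropout with baseline carried, the error in the cases examined ran from about 1% to well above 30%. A method that behaves this way cannot be called conservative for this test.

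**What to change.** For the 12-week yoga–PT comparison, make a missing-at-random method primary. Two choices are acceptable:

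- a likelihood-based repeated-measures model on the observed baseline, 6- and 12-week data with unstructured covariance, reading off the week-12 difference and its confidence interval (the approach of the Maintenance Phase section); or
- the multiple imputation already planned, promoted from comparison to primary and freed from the 10% trigger.

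Move LOCF to a sensitivity analysis and delete the conservative justification for the non-inferiority test. Add a delta-adjusted imputation that makes yoga dropouts progressively worse, to show how far missing at random must fail before the conclusion changes.

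The cost is a little more analysis work and possibly a slightly wider interval. No new data or participants are needed. The article describes the trial as still recruiting, so the change can be made before unblinding.

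### Looking at the pattern of missing data cannot show whether dropout is non-ignorable, so the one step aimed at that risk cannot do its job

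*Protocol article*

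**What the plan says.** The Data analysis section sets out three steps for missing outcomes.

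1. Last value carried forward is the main method: the "approach will be used to fill in missing outcome variables; this approach reflects an analysis of the last known value of the outcomes".
2. Multiple imputation is added depending on how much is missing. If the amount "is substantial (i.e., >10%), we will perform an analysis based on multiple imputation for comparison".
3. The pattern is then reviewed: "We will also examine the pattern of missing data in order to discern whether the missing data mechanism could be non-ignorable". No test, variable list, threshold or consequence is attached.

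The Maintenance Phase models take a separate route: "No missing data will be replaced in these longitudinal analyses", and "All available patient data can be included and the analysis will be considered to be unbiased under a" missing-at-random mechanism.

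For the primary 12-week comparison, "a one-sided α = 0.05 level two-sample *t*-test will be used to determine if yoga is non-inferior to PT". The Sample size considerations section sets the margins: "using a 1.0 point non-inferiority margin for pain is reasonable" and "choosing a non-inferiority margin of 1.5 for function is reasonable". It also allows for 20% dropout.

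**The concern.** Missingness is non-ignorable when, given everything observed, the chance of being missing still depends on the value that was not seen. Before week 12 the article schedules outcomes at baseline and week 6 only. A review of missing-data patterns can therefore use arm, baseline information and week-6 scores, but not the missing week-12 scores.

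An association between dropout and week-6 score shows that missingness is not completely random. It does not show that it is non-ignorable. The absence of an association does not show that it is ignorable. The sentence gives the review a question that its inputs cannot answer.

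The trial's main claim is non-inferiority of yoga to physical therapy (PT). If yoga participants who are doing badly are the ones without a week-12 score, yoga looks better than it is and the error runs towards the claim. A report that found no pattern and took this as evidence against non-ignorable dropout would reassure without grounds.

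**Working it through.** **Inputs.** From Sample size considerations: 128 per main arm, 20% dropout, SD of change 2.5 (pain) and 4.35 (RMDQ), margins 1.0 and 1.5, minimal clinically significant differences 2.0 and 3.0, one-sided α 0.05. From Data collection: visits at baseline, 6 and 12 weeks in the Treatment Phase.

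**The plan's own figures.** Power ≈ Φ(margin × √(n/2) / SD − 1.645).
- Pain, n = 108: 1.0 × √54 / 2.5 = 2.939; 2.939 − 1.645 = 1.294; power 90.2% (stated 90%).
- Function, n = 107: 1.5 × √53.5 / 4.35 = 2.522; 2.522 − 1.645 = 0.877; power 81.0% (stated 81%).

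Both reproduce. The article gives no figure for the pattern review.

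**Why the review cannot answer its question.** Take any set of observed data with 20% of yoga week-12 scores missing, and compare two situations.
- Situation 1: the missing scores follow the prediction from arm, baseline and week 6 (missing at random).
- Situation 2: each missing score is worse than that by δ (non-ignorable).

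The observed data are the same in both, so every pattern review and every fixed analysis, including last value carried forward, gives the same result. The true yoga mean differs by 0.20 × δ:
- Pain, δ = 2.0: 0.20 × 2.0 = 0.40 points, 40% of the 1.0 margin.
- RMDQ, δ = 3.0: 0.20 × 3.0 = 0.60 points, 40% of the 1.5 margin.

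**Could shifts of that size change a conclusion?** Treat all 128 per arm as observed, which overstates precision. SE = SD × √(2/128) = SD × 0.125.
- Pain: SE 0.3125; 1.645 × 0.3125 = 0.514. Non-inferiority is shown if the estimated yoga deficit is below 1.0 − 0.514 = 0.486. A 0.40 shift overturns any result above 0.086.
- RMDQ: SE 0.544; 1.645 × 0.544 = 0.894. The limit is 1.5 − 0.894 = 0.606. A 0.60 shift overturns any result above about 0.006.

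**Illustration by simulation.** Pain, 128 per arm, about 20% missing, true yoga deficit set at the 1.0 margin, 1,500 trials per mechanism. Assumed, not from the article: week-6/week-12 correlation 0.5, half of the deficit present at week 6, logistic dropout models. The pattern review is represented by a likelihood-ratio test at 0.05 of missingness on arm, week-6 change and their interaction. The two non-ignorable mechanisms remove poor responders from yoga and good responders from PT.

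| Dropout mechanism | Pattern found | Estimate assuming missing at random | Estimate, last value carried forward | False non-inferiority, last value carried forward (nominal 5%) |
|---|---|---|---|---|
| Completely random | 5% | 1.00 | 0.90 | 9.7% |
| At random, given week 6 | 99% | 1.00 | 0.93 | 8.5% |
| Non-ignorable, on the part of week 12 not predicted by week 6 | 5% | 0.25 | 0.30 | 73% |
| Non-ignorable, on the week-12 value itself | 64% | 0.32 | 0.54 | 44% |

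A second set of simulations (correlation 0.6, 3,000 single arms, t-test of week-6 score by missingness) found a pattern in 4%, 92%, 5% and 49% for the same four kinds of mechanism. Bias of the regression-imputed mean was 0.00, 0.00, −0.11 and −0.09 SD. For pain, 0.11 × 2.5 ≈ 0.28 points in one arm.

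A pattern appeared most often where an analysis assuming missing at random was unbiased. It appeared no more often than chance in one setting where that analysis was badly biased.

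**The case against.** The strongest reply is that the article defines no check at all. It speaks only of whether the mechanism could be non-ignorable, which may be read as a plausibility judgement, and no analysis depends on the outcome. Multiple imputation is tied to the amount missing, so at the expected 20% it would run whatever the review showed. This stands as far as it goes: the tests simulated above are stand-ins, and their rates are not properties of the trial's plan. It does not rescue the sentence, because even a plausibility judgement about non-ignorability cannot be drawn from the observed pattern alone.

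Four stronger readings are tempting, and the document does not support them.

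- A reader might infer that the review raises alarms only for harmless dropout and stays silent whenever dropout would bias the result. When dropout depends on the week-12 value itself, a pattern appeared in 49% and 64% of simulations. It would still look like missing-at-random dropout. Nor is missing-at-random dropout harmless under last value carried forward, where false non-inferiority was 8.5% to 9.7% in this setting.
- A reader might take 0.28 points, 73% or 44% as forecasts. The first is the bias of a regression-imputed mean in one arm, not of the planned primary method. The other two come from strong dropout in opposite directions by arm. Similar dropout in both arms would largely cancel.
- A reader might fault the article simply for lacking a tipping-point analysis. The statistical analysis plan is not shown and may contain one, so absence alone is not the point.
- A reader might extend the criticism to the Maintenance Phase models. The sentence there is correctly conditional on missing at random and contains no error.

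**Conclusion.** The point holds: the article states a purpose for the pattern review that the review cannot serve. That rests on identifiability alone and needs no assumption about correlation or dropout strength. It is also the only step in the article directed at non-ignorable dropout. Last value carried forward imposes one fixed assumption, multiple imputation as usually run assumes missing at random, and so do the longitudinal models.

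The size of any bias is unknown. What can be said is that, at 20% missing in yoga, shifts up to the protocol's own minimal differences move the yoga mean by up to 40% of either margin. That could decide a non-inferiority result, and no inspection of the observed pattern would reveal it. This merits a change to the plan. It does not show that the trial's conclusion will be wrong.

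**What to change.** Keep the pattern review, but describe it as descriptive: how many are missing, when, in which arm, and with what baseline and week-6 scores. Remove the claim that it can discern non-ignorability.

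Address non-ignorability with a delta-adjusted (tipping-point) multiple imputation for both co-primary endpoints. Impute week-12 changes under missing at random, then worsen the imputed yoga changes in steps over a stated range, for example 0 to 2.0 points for pain and 0 to 3.0 points for RMDQ, the protocol's own minimal differences. Repeat the non-inferiority test at each step and report the shift at which non-inferiority is lost. Fix the range and steps before unblinding. If the statistical analysis plan already contains such an analysis, it is enough to refer to it and correct the sentence.

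The cost is a little more analysis, with imputation the plan already foresees and no new data. The downside is that the report may show the non-inferiority conclusion to be fragile.
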